## Abstract

**ABSTRACT:**

**Introduction:**

Young people (YP) whose parents have depression are at elevated risk for developing depression themselves and could benefit from preventive interventions. However, when parents are in a depressive episode, this reduces the effects of psychological interventions for depression in YP. Moreover, parental depression is often managed suboptimally in usual care. There is, therefore, a case for identifying and optimising parental depression treatment to enhance the effectiveness of psychological preventive interventions for depression in YP.

**Methods and analysis:**

This is a randomised controlled trial (Skills for adolescent WELLbeing) to determine the effectiveness of a cognitive behavioural therapy (CBT) intervention compared with usual care in increasing the time to a major depressive episode in YP by 9-month follow-up (primary outcome). The intervention offers a 12-week treatment-optimisation phase for parents depressed at study entry, followed by randomisation of the young person to a small group manualised online CBT programme facilitated by a therapist. YP allocated to the intervention will receive eight weekly sessions plus three monthly continuation sessions. Secondary outcomes include the number of depression-free weeks, mental health symptoms and functioning. Mechanisms of intervention action will be assessed with mediation analysis of quantitative data and thematic analysis of qualitative interviews. Participants (parents/carers with depression and their children aged 13–19 years) will be identified through existing cohorts of adults with depression, from primary care through health boards in Wales and England, UK, schools and advertising including via social media.

**Ethics and dissemination:**

The trial has received ethical approval from Wales NHS Research Ethics Committee (REC) 5, the Health Research Authority and Health and Care Research Wales (IRAS 305331; REC 22/WA/0254). This manuscript is based on V.5.7 of the protocol (17 January 2025). Findings will be disseminated in peer-reviewed journals and conferences. Reports and social media messages will be used to disseminate findings to the wider public.

**Trial registration number:**

ISRCTN13924193 (date registered: 15 March 2023).

STRENGTHS AND LIMITATIONS OF THIS STUDYThis is a large-scale clinical trial of a preventive intervention, Skills for adolescent WELLbeing (SWELL), adapted from an existing evidence-based cognitive behavioural therapy manual and further developed with young people.The study design incorporates treatment optimisation for parents who are in a depressive episode at study entry.Rigorous trial methodology will be used.The research design does not allow the effects of parent treatment optimisation and the SWELL intervention on outcomes in the young person to be examined separately.For ethical and pragmatic reasons, participants are free to start any new treatment during the study period, meaning that external treatment use must be evaluated as an explanation of any differences between trial arms.

## Introduction

 Depressive symptoms and major depressive disorder (MDD) are common and often emerge during adolescence.^1^ They are associated with poor health, social and educational outcomes,^2 3^ and rates have risen sharply.^4 5^ Depression in young people (YP; aged 16–25 years)^6^ is therefore a major public health concern that requires effective, scalable prevention strategies.

In the UK, approximately 25–30% of children have a parent with treated depression.^7 8^ Having a depressed parent increases the risk of MDD by 3–10-fold in YP.^9 10^ YP with depressed parents are therefore an important high-risk group that may benefit from targeted prevention programmes.^11^

Most intervention research in this area has examined cognitive behavioural therapy (CBT) approaches.^12^,^14^ A promising example is the group-based *Coping with Stress* (CwS) programme, comprising an ‘acute phase’ (eight weekly sessions) and a ‘continuation phase’ (six monthly sessions).^15^,^17^ CwS had the largest effect size in preventing depression among YP in a Cochrane review.^12^ Moreover, these effects were relatively long-lasting (6 years).^12 17^

A US multisite effectiveness randomised controlled trial (RCT) of CwS used a combined selective and indicated prevention approach focusing on YP with parental history of depression *and* either a personal history of depression and/or elevated depression symptoms.^16^ Overall, CwS significantly reduced the risk of MDD onset in YP compared with usual care. However, a weaker main effect was found for YP whose index parent was experiencing a current depressive episode at baseline. This is consistent with other studies showing (1) current parental depression moderates CBT outcomes for depressed YP^18^ and (2) maternal depression remission is associated with decreased psychiatric symptoms and improved functioning in YP.^19 20^ Therefore, there is a case for identifying and treating parental depression to improve outcomes of preventive interventions for depressed YP.

### Study objectives

This paper describes the protocol of a study funded by the Wolfson Foundation. The study was designed to test the effectiveness of an adapted version of CwS, called Skills for adolescent WELLbeing (SWELL). The goal of the SWELL intervention is to prevent the onset/recurrence of MDD in YP at high-familial risk of depression. When designing the study, several adaptations were made with input from the trial team, the trial management group (TMG), the original intervention developers, clinicians and YP, and the potential impact of these was considered.^21 22^ The main adaptation involved including treatment optimisation for parents in a depressive episode at study entry before randomisation of the YP. This adaptation was intended to maximise the effectiveness of the intervention for YP. Although the addition of an intergenerational component might add to the burden of delivery, we judged that the potential benefits of adding parent treatment optimisation (PTO) outweighed the risk of increasing complexity of delivery.

We also made two main adaptations to the delivery of CwS. First, we reduced the number of continuation sessions from six to three. This was done with future implementation in mind, given that YP depressive symptomatology is common and access to psychological interventions is limited.^23^ As SWELL is intended to be a preventive intervention, we decided the content could be delivered effectively over a shorter period, reducing the burden of participation for YP. Indeed, a secondary analysis of CwS showed that efficacy remained with partial completion of intervention sessions.^24^ Second, we adapted the intervention for online delivery, due to scalability considerations about possible future implementation in healthcare settings. Evidence indicates that online psychological interventions are as effective as face-to-face formats,^25^ especially when this is facilitated by a therapist.^26^

In terms of presentation, we made minor updates to the materials included in the original CwS workbook. This included the use of more contemporary comic strips to illustrate key learning points. We also translated the YP workbook into Welsh to create a bilingual resource (although all intervention groups will be delivered in English during the planned trial). The adaptations described were judged necessary for a UK context with a view to future implementation in NHS settings.^21 22^

Given the amendments made to the intervention, we will carry out interviews with therapists following completion of the first two YP intervention groups and analyse with rapid content analysis.^27^ This will inform if minor procedural updates are required to ensure feasible and accessible ongoing delivery for the remainder of the trial.

### Aims

The primary aim is to test the effectiveness of SWELL in increasing the time-to-onset of YP MDD by 9-month follow-up. We will also examine the effects of the intervention on secondary outcomes including depression-free days, depression risk score, mental health problem symptoms, functioning and quality of life. A nested process evaluation will assess fidelity, adherence, the impact of adaptations on effectiveness and implementation and possible intervention mechanisms. We will undertake quantitative analyses of potential intervention mediators (eg, dysfunctional attitudes, self-efficacy) and exploratory analysis of factors that might modify effectiveness (eg, parent depression status).

## Methods and analysis

This study protocol is based on the Standard Protocol Items: Recommendations for Interventional Trials 2013 statement (online supplemental material 1).

### Trial design

This is a multisite, two-arm, parallel-group effectiveness RCT with assessors blinded to allocation. YP will be randomised 1:1 to the intervention condition (the SWELL programme plus usual care) or the usual care only condition. Given that most YP do not receive preventive interventions, usual care is the appropriate comparator. The method of randomisation will be simple-permuted-block randomisation stratified by site, with the unit of randomisation being the YP (online supplemental material 2).

### Eligibility criteria

These are outlined in box 1 and involve identifying a group of YP aged 13–19 years at high risk of depression (depression in a parent/carer plus YP current elevated symptoms/a past depressive episode). Other eligibility criteria will ensure YP can participate fully and that the parent/carer will consider engaging with PTO. We will also ensure parents do not have additional mental health diagnoses likely to impact on the appropriateness and effectiveness of PTO (eg, bipolar disorder/psychosis).^28 29^

Box 1Eligibility criteria
**Inclusion criteria**
Young person is aged 13–19 years.A young person is experiencing current elevated depressive symptoms as indexed by a Centre for Epidemiological Studies-Depression scale score of ≥16 and/or has a history of a Diagnostic and Statistical Manual of Mental Disorders-Fifth Edition major depressive episode but does not have a current diagnosis of depression from a doctor or health professional at screening.Young person is living with a parent (biological or non-biological) who has a history of depression (at least one previous episode) who will consider engaging with a depression treatment plan.Both the young person and parent have access to the internet via a desktop/laptop/phone/tablet and have a valid email address or mobile phone number.Both the young person and parent can complete trial activities as specified in the protocol, for example, sufficient understanding of the English language, absence of learning disability that would impair ability to participate and for the young person, ability to participate in small group cognitive behavioural therapy (CBT) sessions.
**Exclusion criteria**
Young person is already receiving specialist treatment for depression (eg, currently on antidepressants or receiving CBT).Young person has a current diagnosis of depression from a doctor or healthcare professional.A young person has been told by a doctor or healthcare professional that they have a diagnosis of bipolar disorder, schizophrenia, psychosis, eating disorder or alcohol/drug dependence.A young person has generalised learning difficulties that, the parent judges, would prevent them from participating in trial activities.Parent has a diagnosis of bipolar disorder, schizophrenia or personality disorder.Parent is receiving treatment from secondary mental health services (eg, community mental health team or psychiatrist).Parent or young person not resident in the UK.

At study enrolment, if the parent is currently depressed at the screening stage, they will be offered PTO. Baseline assessments will follow completion of PTO (or immediately if the parent refuses the PTO offer), and the YP will be randomised.

### Study setting

The trial will be conducted by Cardiff University and supported by University Health Boards (UHBs) in Wales and Clinical Research Networks (CRNs) in England. UHBs and CRNs will facilitate recruitment via general practices (GPs) and mental health services. Secondary schools will also be approached to support recruitment.

### Recruitment

We will recruit via: (1) existing cohorts (https://www.ncmh.info/, https://gladstudy.org.uk/), (2) primary care and mental health services, (3) schools and (4) advertising (eg, posters/leaflets, videos) in health/community settings. Standard emails/letters/text messages with options to respond via multiple methods (study website/email/telephone) will be used to distribute study information. To help ensure a diverse sample, we intend to minimise inclusion criteria and recruit in socioeconomically diverse areas. Interested individuals will be asked to complete an online form to register interest and provide contact details. They will be contacted by telephone/videocall to complete screening with a researcher (and ask any questions). Once confirmed as eligible, the parent and YP will complete the appropriate informed consent/assent forms via phone/videocall with a researcher (online supplemental material 3). Of parents who register an interest, we estimate 25% will have a child who fulfils the eligibility criteria (ie, they have a history of depression/currently elevated symptoms) based on data from this population.^30^,^32^ Recruitment progress will be monitored regularly against expected targets.

### Changes to the trial since recruitment began

In consultation with the study TMG and trial steering committee (TSC), minor changes were made to broaden inclusion criteria to better reflect how the intervention would be delivered in practice (online supplemental material 4; Analyses).

### Sample size

We aim to recruit 400 YP and parents/carers, based on a previous study^17^ and sample size calculations. We allow for 10% loss to follow-up based on previous studies of this population and depressed YP.^1630^,^32^ The effect size observed in the study by Garber *et al*^16^ was a HR of 0.63. We expect the effect of the intervention in this RCT to be slightly greater than this due to the addition of PTO before randomisation. We therefore define the minimum clinically important difference for this study as an HR of at least 0.60 (equivalent to an 11% difference in MDD between study arms). With a sample size of up to 400 randomised participants, we estimate statistical power as 79.9% to detect a difference of at least HR=0.60 between study arms, with an assumed 10% attrition rate at 9 months, expected event rate probabilities at follow-up of 0.327 (control) and 0.211 (intervention) based on^17^ a one-sided alpha of 0.05. A HR of 0.56 (equivalent to a 12% difference between study arms) will attain 87.0% power. A STATA V.17 programme was used for this estimation.^33^

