### Analyses

The flow of participants through the trial will be presented as a Consolidated Standards of Reporting Trials diagram. Baseline demographic data will be presented for all consented and randomised participants, and patterns of attrition will be examined.

The primary analysis will be time-to-event analysis of the primary outcome (time to the first depressive episode collected at 9-month follow-up) and will use the complete case dataset. However, multiple imputation will be considered as a sensitivity analysis to examine possible dropout bias in the treatment effect estimate. Consistent with clinical practice, depression in the YP will be defined as YP depression reported by either parent/YP with a planned sensitivity check for YP report only. A Cox regression model will be used to determine the difference between trial arms, the HR and 95% CI. We will investigate whether a random effect to account for the group delivery clustering in the intervention arm needs to be included in the primary model. If the effect of the clustering is negligible, this will be excluded. Assumptions of the model (eg, constant hazard) will be checked to ensure model validity. Prespecified subgroups to be compared descriptively include those defined by baseline characteristics of the YP (eg, comorbidity) and parents (eg, depression status at randomisation). External treatment use will also be compared descriptively across study arms, and its effect will be evaluated by including this as a time-varying covariate in the Cox model.

Possible effect modification (eg, by PTO response, baseline demographic factors) will be investigated by including an arm*modifier interaction term. Mediation analyses will examine the effects of potential mediators (eg, improved problem-solving skills, improved parent-child relationship) on the primary outcome via inclusion of the mediator predictor in the primary model.

A sensitivity check will explore the effect of changes to inclusion criteria on the effectiveness of the intervention (online supplemental material 4). Only 20 participants were consented prior to the implementation of these changes, meaning their inclusion is unlikely to influence the main study findings in a substantial way.

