### Trial status

Recruitment started on 21 August 2023, the first participant was consented on 19 September 2023 and 267 participants had been recruited by 02 June 2025. Recruitment is planned to be completed by August 2025 with analysis and dissemination between September 2025 and February 2027. Cardiff University is the study sponsor (ref: SPON1902-22) and the study contact for enquiries is [contact].

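### The stated power (79.9% and 87.0%) is for a one-sided 5% test; for the planned 95% CI to exclude 1 it is about 70% and 79%

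*Protocol article*

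**What the plan says.** The Sample size section of the protocol article states: "we estimate statistical power as 79.9% to detect a difference of at least HR=0.60 between study arms". The basis is up to 400 randomised, 10% attrition at 9 months, event probabilities of 0.327 (control) and 0.211 (intervention), and "a one-sided alpha of 0.05". The same section gives 87.0% power for an HR of 0.56. It defines the target difference as "an HR of at least 0.60 (equivalent to an 11% difference in MDD between study arms". Allocation is equal (Trial design: "YP will be randomised 1:1 to the intervention condition").

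On the primary analysis, the Analyses section says: "A Cox regression model will be used to determine the difference between trial arms, the HR and 95% CI". It also plans 95% CIs for all outcomes. Neither the Aims nor the Analyses section mentions a one-sided test, a 90% CI or a one-sided confidence bound. The article gives no reason for choosing a one-sided alpha and no rule linking that alpha to the 95% CI.

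**The concern.** A one-sided 5% test pairs with a 90% CI or a one-sided 95% bound. A 95% CI pairs with two-sided 5%, that is, 2.5% in the direction of benefit. The article fixes one standard for sizing the trial and another for presenting the primary result, and does not say which decides the conclusion.

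Three things are at stake:

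- The power figures do not describe the chance that the published interval will exclude no effect. That chance is about ten percentage points lower at HR 0.60 and about eight lower at HR 0.56.
- The false-positive rate for a claim of benefit is 5% under the design alpha and 2.5% if the 95% CI is the criterion.
- There is a band of results in which the test and the interval disagree. With no rule fixed beforehand, the criterion could be chosen once the result is known.

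**Working it through.** **Inputs** (Sample size and Trial design sections): 400 randomised 1:1; 10% attrition, so 360 evaluable and 180 per arm; event probabilities 0.327 and 0.211; one-sided alpha 0.05. Critical values: z = 1.645 (one-sided 5%) and z = 1.960 (two-sided 5%).

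**Expected events at HR 0.60.** Control 180 × 0.327 = 58.9; intervention 180 × 0.211 = 38.0; total 96.8. The inputs cohere: under proportional hazards the two probabilities imply HR = ln(1 − 0.211) / ln(1 − 0.327) = 0.598.

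**Reproducing 79.9%.** Power = Φ(signal − critical value), with |ln 0.60| = 0.511.

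- Schoenfeld: signal = √(96.8/4) × 0.511 = 2.51; one-sided power 80.8%.
- Freedman: signal = √96.8 × (1 − 0.60)/(1 + 0.60) = 2.46; one-sided power 79.3%.
- Arm-specific events: SE(ln HR) = √(1/58.9 + 1/38.0) = 0.208; signal = 0.511/0.208 = 2.45; one-sided power 79.1%.
- Two proportions, 180 per arm: one-sided power 80.1%.

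The range of 79.1–80.8% brackets the stated 79.9%.

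**Reproducing 87.0%.** At HR 0.56 the implied intervention probability is 1 − (1 − 0.327)^0.56 = 0.199, giving 180 × (0.327 + 0.199) = 94.7 events. One-sided power by the same four methods is 88.0%, 86.4%, 86.2% and 87.0%.

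**Same inputs at the level of the 95% CI.** Only the critical value changes, from 1.645 to 1.960.

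| | HR 0.60 | HR 0.56 |
|---|---|---|
| Stated, one-sided 5% | 79.9% | 87.0% |
| Schoenfeld, two-sided 5% | 71.0% | 80.5% |
| Freedman, two-sided 5% | 69.2% | 78.4% |
| Arm-specific events, two-sided 5% | 69.0% | 78.1% |
| Two proportions, two-sided 5% | 70.1% | 79.1% |

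The stated figures can also be converted directly, without choosing a formula. Power of 79.9% implies a signal of 0.838 + 1.645 = 2.483, and Φ(2.483 − 1.960) = 69.9%. Power of 87.0% implies 1.126 + 1.645 = 2.771, and Φ(2.771 − 1.960) = 79.1%.

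**Where test and interval disagree.** With SE(ln HR) = 0.208, the one-sided 5% test is passed when the observed HR is below exp(−1.645 × 0.208) = 0.71. The 95% CI excludes 1 only when it is below exp(−1.960 × 0.208) = 0.665. If the true HR is 0.60, the estimate falls between these limits in about 79.1 − 69.0 = 10% of trials.

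**Sensitivity to attrition at HR 0.60.** If drop-outs contribute about half their follow-up (an assumption, about 102 events), two-sided power is 71.5–73.4%. With no attrition (about 108 events) it is 73.7–75.5%. Neither reaches 79.9%.

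**The case against.** The strongest reply is that nothing has been miscalculated or hidden. The one-sided alpha stands in the same sentence as the power figure, the figure is right for that alpha, and the primary aim is directional (a longer time to onset). A 95% CI can be reported as an estimate beside a one-sided test, and the Analyses section never says that success means the interval excludes 1. How test and interval combine is often left to the analysis plan, which is not shown. A two-sided test is also only one remedy, and adopting it changes a declared design alpha after most of the sample has been recruited.

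Much of this stands. The 79.9% is not an arithmetic error, and 70% is not a correction of it; it is the power for a different criterion. The sponsor may defend the one-sided test, and the fix must leave that route open.

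It does not remove the inconsistency. The article does not simply leave the level to the analysis plan: it states both the alpha and the interval, and they belong to different tests. It does not call the 95% CI descriptive, and it names no interval that matches the design alpha. A reader who sees only the HR and 95% CI will judge the trial by whether the interval excludes 1, and the stated power does not apply to that judgement.

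**Conclusion.** The inconsistency is real and should be resolved before the primary analysis. For the 95% CI to exclude 1, power is about 69–71% at HR 0.60 (stated 79.9%) and about 78–81% at HR 0.56 (stated 87.0%). An observed HR of roughly 0.67 to 0.71 would be significant at the design alpha while the 95% CI includes 1. These figures assume 400 randomised, 10% attrition with drop-outs contributing no events, the stated event probabilities and proportional hazards. They make no allowance for clustering by therapy group, which would lower power further.

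Two further inferences are tempting but not supported:

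- A reader might infer from the Trial status section ("267 participants had been recruited by 02 June 2025" and "Recruitment is planned to be completed by August 2025") that 400 will not be reached and that power is lower still. That is a straight-line forecast. The article gives no monthly accrual, the eligibility criteria were broadened after recruitment began, and the sample size is worded as a ceiling. It does not show that the Sample size section is wrong.
- A reader might infer that 0.60 is mislabelled as the minimum clinically important difference because a weaker effect, 0.63, is cited. The article reports 0.63 as the effect observed in an earlier trial and does not say that it would be worthwhile.

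**What to change.** Before the primary analysis, state in the protocol and the statistical analysis plan that the primary test is two-sided at 5%, matching the 95% CI. Restate power with 400 randomised as about 70% at HR 0.60 and about 79% at HR 0.56.

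If the one-sided 5% test is kept, give the reason for it, name the 90% CI or one-sided 95% bound as the interval on which the decision rests, say how a 95% CI that includes 1 will then be described, and give the two-sided power beside the stated figures.

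The cost is wording and a less favourable power figure. The sample size need not change. For context, 80% two-sided power at HR 0.60 would take 121 (Schoenfeld) to 126 (Freedman) events. Dividing by the mean event probability of 0.269 and by 0.9 for attrition gives about 500 to 520 randomised. That is not proposed here; it shows what the choice of alpha is worth.
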